##### Sampling Method, Recruitment, and Data Collection Procedure

We will conduct a quasi-experimental (ie, rather than a randomized) study given that our intervention will depend on whether an older adult’s FMG includes a participating pharmacist (intervention group) or not (control group).

##### Sample Size Calculation

According to prior estimates provided by the CI(U)SSS, about 50 older adults may be targeted for participation per FMG per year. Considering that the on-site presence of FMG pharmacists is on average 2 to 3 days a week [11,12], it should be feasible to include approximately 40 older adults per FMG. By setting our intercluster correlation coefficient at 0.005 (conservative), the number of clusters (FMGs) at 5 intervention and 5 control FMGs, and at 40 older adults per FMG, we expect to be able to detect a difference of 1 medication per older adults between the beginning and the end of the intervention, between the 2 groups, with a power of 83%. Therefore, we have planned a 12-month inclusion period, corresponding to recruiting approximately 1 person per week per FMG. The inclusion date will be when the reference to the pharmacist was made. For control FMGs, we will consult electronic medical records and FMG health care professionals to identify all older adults who meet the inclusion criteria. Since there will be no reference to the pharmacist for these individuals, the inclusion date will be the date of identification by the FMG. For those receiving home care services, the inclusion date will be the first home visit following the start of the study.

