## Results

All study materials (questionnaires, patients’ recruitment tools, and training documents) have been developed in collaboration with clinicians and patient partners. As of September 2022, 13 FMGs have agreed to participate in the GPS project (11 implementing the intervention and 2 as controls). We have yet to recruit more FMGs that will be part of the control group. Recruitment of older adults began in September 2021, when the project was launched. We had planned 12 months for the inclusion of eligible older adults. As of September 2022, a total of 100 participants had been enrolled and the follow-up was completed for 23 of them. Data collection will take approximately 18 months, and data analysis and synthesis of the results will take another 9 months. Knowledge transfer/mentoring sessions will be organized regularly during the implementation period (ten 1-hour meetings in each CI[U]SSS have been realized as of September 2022) and are also planned after the end of the GPS study (approximatively 6 months). These sessions are open to FMG pharmacists, physicians, mentors (physicians and pharmacists with geriatric expertise), and research team members and comprise short presentations of specific clinical interest, summaries of issues surrounding the study methods and procedures, as well as an occasion for an exchange between all these persons on clinical and research questions.

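### The 83% power depends on a near-zero ICC called conservative without support and on a 5:5 × 40 design not in place after the planned 12 months; it is not restated

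*Protocol article*

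**What the plan says.** Protocol article, Sample Size Calculation: the calculation proceeds "By setting our intercluster correlation coefficient at 0.005 (conservative), the number of clusters (FMGs) at 5 intervention and 5 control FMGs". Each FMG is to contribute 40 patients, that is 10 × 40 = 400 patients. The stated target is to "detect a difference of 1 medication per older adults between the beginning and the end of the intervention". The power given for this comparison of the intervention and control arms is 83%. Inclusion is planned over 12 months. No source is given for the ICC.

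Protocol article, Results: recruitment of patients began in September 2021. The position reported for September 2022 is that "13 FMGs have agreed to participate in the GPS project (11 implementing the intervention and 2 as controls"), and "a total of 100 participants had been enrolled and the follow-up was completed for 23 of them". The same section says that further control FMGs are still to be recruited. It gives no revised power or sample size.

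Protocol article, Study Setting and Discussion: FMGs join at their own convenience in two territories, one metropolitan and one mixed urban and rural. Each FMG or home care team will adapt the intervention, which may therefore vary slightly between sites.

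**The concern.** A conservative planning value errs in the direction that lowers power. For an ICC that direction is up, and 0.005 lies close to zero. The article's own account of local adaptation, voluntary participation and two different territories gives reason to expect some variation between FMGs, so the label needs support that the article does not give.

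The second part concerns the design. The 83% is conditional on equal allocation of FMGs and 40 patients in each, recruited in 12 months. At the end of those 12 months the FMGs stood at 11:2 and the patients at a quarter of the target. With few control clusters, precision is limited by the small arm however many patients the intervention arm adds.

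At stake is the reading of a null primary result. If 83% remains the only published figure, such a result could be taken as evidence against a one-medication effect when the trial may have had much less power to detect it.

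**Working it through.** **Inputs from the article.** Difference 1 medication; ICC 0.005; 5:5 FMGs; m = 40 per FMG (200 per arm); power 83%. Status at September 2022: 11:2 FMGs, 100 patients.

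**Assumptions.** Alpha 0.05, two-sided. The SD of change is not printed, so it is solved from the stated power. The ICCs of 0.01, 0.02 and 0.05 are illustrative and do not come from the article.

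**Formulas.** DE = 1 + (m − 1) × ICC. SE = SD × √(DE/n₁ + DE/n₂). Power = Φ(1/SE − 1.96). Difference detectable at 83% power = (1.96 + 0.954) × SE.

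**Step 1: the stated figure.** DE = 1 + 39 × 0.005 = 1.195, so the effective n per arm is 200/1.195 ≈ 167. Power of 83% requires SE = 1/(1.96 + 0.954) = 0.343, hence SD = 0.343/√(2 × 1.195/200) = 3.14. If the authors instead used a t reference with 10 − 2 = 8 df, the implied SD is 2.75. The 83% is therefore attainable, but because the SD is solved from it, this is not an independent check.

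**Step 2: sensitivity to the ICC at 5:5 × 40.**

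| ICC | DE | SE (SD 3.14) | Power, z (SD 3.14) | Power, t on 8 df (SD 2.75) |
|---|---|---|---|---|
| 0 | 1.000 | 0.314 | 89% | 89% |
| 0.005 | 1.195 | 0.343 | 83% | 83% |
| 0.01 | 1.390 | 0.370 | 77% | 77% |
| 0.02 | 1.780 | 0.419 | 67% | 67% |
| 0.05 | 2.950 | 0.539 | 46% | 46% |

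The assumed ICC costs only 6 points against no clustering at all. The fall at larger ICCs is the same whichever reference distribution lies behind the 83%.

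**Step 3: allocation and size, at the plan's own ICC of 0.005 (SD 3.14, z).**

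| Scenario | n intervention : control | DE | SE | Power | Detectable at 83% |
|---|---|---|---|---|---|
| 5:5 × 40 (planned) | 200 : 200 | 1.195 | 0.343 | 83% | 1.0 |
| 11:2 × 40 | 440 : 80 | 1.195 | 0.417 | 67% | 1.2 |
| 11:2, 400 in total (30.8 per FMG) | 338 : 62 | 1.149 | 0.466 | 57% | 1.4 |
| 11:2, 100 in total, even spread (7.7 per FMG) | 85 : 15 | 1.033 | 0.884 | 20% | 2.6 |
| 11:2, 100 in total, 50 per arm | 50 : 50 | 1.018 and 1.12 | 0.649 | 34% | 1.9 |
| 11:5 × 25 (400 in total) | 275 : 125 | 1.120 | 0.358 | 80% | 1.04 |

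The article does not give the split of the 100 patients by arm. The last two 100-patient rows cover an even spread over FMGs and an equal split between arms. With the t-based SD of 2.75 and (number of FMGs − 2) df, the 11:2 rows with 40 per FMG, 400 in total and 100 evenly spread become 70%, 61% and 22%, and 11:5 × 25 becomes 84%.

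**The case against.** The strongest reply is that no error has been shown. The SD is solved so that 83% comes out, which agrees with the stated figure and cannot refute it. That stands.

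A reader might infer that 0.005 is wrongly called conservative. The documents do not support this. They contain no ICC estimate for this outcome, a change score may have a different ICC from a level, and the Discussion describes the expected variation as slight. What can be said is that the label has no support in the article.

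A reader might also infer that the authors ignored the small number of clusters. With an SD of 3.14, a t reference on 8 df would give 72% at ICC 0.005. But the article never says that a normal approximation was used. If the 83% was already t-based, there is no loss at the planned design. Nor is the absence of the SD, alpha and pre-post correlation a fault in a condensed article.

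Finally, a reader might take 11:2 and 100 patients as the trial's design, with power of about 20%. The Results section is a dated status report, control recruitment was still open, and the Discussion discloses delays and recruitment difficulties. The 83% is stated for 5:5 × 40 and is nowhere claimed for the September 2022 position. If controls reached the planned five, power would be back to about 80% with 25 patients per FMG and 93% with 40.

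What the reply does not remove is that the label points the reader the wrong way without evidence, and that an article reporting so large a departure from its design assumptions leaves 83% as its only power figure.

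**Conclusion.** The point holds in limited form. The 83% is conditional on an ICC whose description as conservative is unsupported, and on an allocation and size not in place when the planned inclusion period had elapsed.

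The sensitivity to the ICC is material: a move from 0.005 to 0.02 costs about 16 points, and a move to 0.05 about 37. The sensitivity to allocation is also material: two control FMGs hold power to about 67% even with 520 patients, more than the 400 planned. The figures for 100 patients (20% to 34%) measure the shortfall to date and do not forecast the final design.

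All of this assumes two-sided alpha 0.05, the SD implied by the stated power, and ICC values above 0.005 chosen for illustration. The ICC results are the same to the nearest point on a z or a t basis. The allocation results on the t basis are 2 to 5 points higher.

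**What to change.** 1. Remove the word conservative, or give a source for the ICC that applies to the change in number of medications.
2. Report power over a range of ICCs, for example 0.005 to 0.05, using cluster-level degrees of freedom (number of FMGs minus 2) and naming the SD on which the figures rest.
3. Restate power and the detectable difference for the FMG numbers, allocation and cluster sizes finally achieved, and report these beside the primary result so that a null finding is not read as coming from an 83%-powered study.
4. Keep further FMG recruitment on the control side, as the article already intends; Step 3 shows that this is where precision is gained.

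Items 1 to 3 cost only rewording and recalculation, and the stated power is likely to be less favourable. Item 4 adds nothing to what is already planned.

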##### Outcomes Measures

The primary outcome measure is the change in the number of prescribed medications. Specifically, (1) the total number of prescribed medications and (2) the number of potentially inappropriate medications according to the Beers criteria [33] will be measured in the intervention and control groups. We will obtain data from patients’ medical records at the beginning (baseline) and 6 months after inclusion in the study.

We will assess several secondary outcome measures. First, a change in the treatment burden level will be measured with the 13-item MTBQ [26,27] in the intervention and control groups at baseline and 6 months follow-up. We will score each item as follows: 0 (not difficult/does not apply), 1 (a little difficult), 2 (quite difficult), 3 (very difficult), and 4 (extremely difficult). We will interpret the scores as suggested by the authors of the original MTBQ instrument: no burden (score 0), low burden (score <10), medium burden (score 10-22), and high burden (score ≥22) [26].

Second, we will measure the quality of life in the intervention and control groups at baseline and 6 months follow-up with the EQ-5D-5L [28]. The descriptive system comprises 5 dimensions: mobility, self-care, usual activities, pain/discomfort, and anxiety/depression. Each dimension has 5 levels: no problems, slight problems, moderate problems, severe problems, and extreme problems. Responses are coded as single-digit numbers expressing the severity level selected in each dimension [28]. The last study outcome is the satisfaction with the care received and access to care. To measure this outcome, the PESQ, validated in Quebec primary care settings, will be used [29]. We have adapted the questions with the author’s approval to consider not only the physician but the whole FMG team.

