### The GPS intervention

First, nurses and physicians in intervention FMGs (exposed) will be asked to refer all older adults undergoing cognitive evaluation OR referred to a memory clinic OR recently diagnosed (<12 months) with a MNCD to the FMG pharmacist. Moreover, home care teams will be asked to refer older adults receiving home care for MNCDs to the FMG pharmacist. FMG pharmacists will perform a medication review. A medication review is a structured and comprehensive evaluation of a patient’s pharmacotherapy with the aim of identifying and resolving problems and improving health outcomes [30]. This medication review involves an interview with each referred older adult, including their caregiver, if applicable, to establish the best possible medication history (BPMH) [31]. The BPMH is a complete documentation of medication therapy, including the name, dose, administration route, and medication administration frequency. To this end, medication information will be validated with at least 1 other reliable data source (eg, community pharmacy records) and documented in the patient’s chart. The pharmacist will then detect medication-related problems [32] by analyzing this information and clinical data using their own judgment or validated criteria [33]. They will establish a care plan and the follow-ups needed with the patient in collaboration with the health care team and the community pharmacist. Pharmacists will also document the number and type of interventions and recommendations made to optimize patients’ pharmacotherapy for 6 months following the medication review. We will offer training and mentoring support to these teams, including pharmacist support for more complex interventions and monthly web-based interdisciplinary meetings.

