### Study Setting

The study will comprise participants from an exposed group of approximately 5 FMGs with attending pharmacists who will implement the intervention and a control group composed of participants from 5 others FMGs without involved pharmacists. FMGs and home care teams will participate at their convenience within 2 Integrated (University) Health and Social Services Centers territories: (1) the *Centre intégré universitaire de santé et de services sociaux* (CIUSSS) *du Nord-de-l’Ile-de-Montréal* (NIM) in a metropolitan area and (2) the *Centre intégré de santé et de services sociaux* (CISSS) *de Chaudière-Appalaches* (CA) in a mixed—urban and rural—area. We used this selection process to facilitate implementation as the intervention teams need to be motivated toward its application and training and mentoring activities. To be eligible for participation, intervention FMGs must have at least 1 participating pharmacist, interested partner nurses, and physicians. Similarly, intervention home care teams must have access to a participating FMG pharmacist and a home care nurse. In contrast, in control FMGs and their home care teams, no FMG pharmacist will be systematically involved in the eligible patients’ trajectory. However, the FMGs must be willing to allow data collection and delay implementing similar interventions within their teams.

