### Data Analysis

In step 1, we will use an intention-to-treat approach to assess the GPS intervention’s effectiveness. The principal analysis will compare the difference (1) in the average number of medications per person between the unexposed and exposed groups according to the study period (baseline and 6 months) and (2) the average number of potentially inappropriate medications per person between the 2 groups, according to the study period, by mixed Poisson repeated measures regression. This type of analysis considers intra-FMG and intraindividual correlations. Contrasts will be built to determine if the average number of medications per person over time differs between the exposed and the unexposed group. Secondary results will be analyzed similarly to compare the MTBQ, PESQ, and EQ-5D-5L scores between the groups exposed and unexposed to the GPS intervention.

Medication data missing at measurement time periods after the initial data collection will be imputed using the last-observation-carried-forward method. Using this method, the potential benefits of the intervention should be underestimated. For participants lost to follow-up regarding the questionnaires, no measures will be imputed at follow-up, but sensitivity analyses may be used in which baseline questionnaires scores could be imputed for follow-up scores. We will perform all analyses with SAS statistical software (SAS Institute Inc).

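### Both primary counts come from the medical chart, but only intervention patients have a verified medication history written into it, so the group-by-time contrast can mix prescribing change with list correction

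*Protocol article*

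**What the plan says.** **Outcome and source.** Under Outcomes Measures, "The primary outcome measure is the change in the number of prescribed medications", specified as the total number and the number that are potentially inappropriate by the Beers criteria. Both groups are measured from patients' "medical records at the beginning (baseline) and 6 months after inclusion in the study".

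**What the intervention does to the record.** Under The GPS intervention, the pharmacist interviews the patient (and caregiver, if any) to obtain a complete medication history. The article then states that "medication information will be validated with at least 1 other reliable data source (eg, community pharmacy records) and documented in the" patient's chart. Pharmacists also document the number and type of their interventions and recommendations for 6 months.

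**What controls get.** Under Study Setting, in control clinics "no FMG pharmacist will be systematically involved in the eligible patients" (the sentence continues with their trajectory).

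**When baseline falls.** Under Sample Size Calculation, for the intervention group, "The inclusion date will be when the reference to the pharmacist was made". For controls, "the inclusion date will be the date of identification by the FMG". For home-care patients it is the first home visit after the study starts.

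**How the effect is estimated.** Under Data Analysis, a mixed Poisson repeated-measures model is used, and "Contrasts will be built to determine if the average number of medications per person over time differs between the exposed and the unexposed group".

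**The concern.** The intervention acts on patients' treatment and also on the document from which treatment is counted. If a chart still lists a drug the patient no longer has prescribed, verification can take one entry off the count with no change in exposure. If the chart lacks a drug the patient is prescribed, verification can add one. In the intervention group such corrections fall between the two readings. In the control group the study prompts no such step at either reading.

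The article gives no rule that separates a corrected entry from a drug actually stopped or started, so both would enter the group-by-time contrast as intervention effect. At stake is the interpretation of both primary outcomes: a difference could partly reflect tidier lists, or a real reduction could be hidden by newly recorded drugs.

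**Working it through.** **Step 1: where the artefact enters.** Let T be the true number of prescribed medications and e the net list error (obsolete entries minus omitted entries), so that the chart count is T + e.

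- Intervention: baseline T0 + e0 before the review. If verification brings the error to about zero, the 6-month count is about T1. Measured change = (T1 − T0) − e0.
- Control: measured change = (T1 − T0) + (e1 − e0), which is the true change if the list error is stable over 6 months.
- Contrast (intervention minus control) = true contrast − e0, with e0 the net error in the intervention charts at baseline.

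A positive e0 (mostly obsolete entries) mimics benefit; a negative e0 (mostly omissions) masks it. Terms for intra-FMG and intraindividual correlation do not remove a mean shift of this kind.

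**Step 2: the plan's own figure.** Inputs from Sample Size Calculation: 5 + 5 FMGs, 40 patients each (200 per group), intracluster correlation 0.005, difference of 1 medication, power 83%. The article states no standard deviation (SD), alpha or sidedness, so the 83% cannot be reproduced directly. It can be inverted.

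- Design effect = 1 + (40 − 1) × 0.005 = 1.195
- Effective n per group = 200 / 1.195 = 167.4
- Implied SD of change, two-sided alpha 0.05 assumed = 1 × √(167.4/2) / (1.960 + 0.954) = 3.14
- Standard error of the contrast = 3.14 × √(2/167.4) = 0.343

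Other assumptions give an SD of 3.52 (one-sided 0.05) or 2.75 (t test with 8 cluster degrees of freedom).

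**Step 3: illustration.** Let b be an assumed net number of entries corrected per intervention patient. With no true effect and net removal, P(reject) = Φ(b/0.343 − 1.960) + Φ(−b/0.343 − 1.960). For b = 0.5, b/0.343 = 1.457, and Φ(−0.503) + Φ(−3.417) ≈ 0.308. With a true effect of 1 and net addition, 1 − b replaces b.

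| Assumed b | False-positive probability (net removal, no true effect) | Power for a true effect of 1 (net addition) |
|---|---|---|
| 0 | 5% | 83% |
| 0.10 | 6% | 75% |
| 0.25 | 11% | 59% |
| 0.50 | 31% | 31% |
| 0.75 | 59% | 11% |
| 1.0 | 83% | 5% |

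The table is a normal approximation for a difference in means, not the planned Poisson model. The last row is true by construction, because a shift equal to the target difference must return the stated power. The table shows sensitivity; it is no evidence about the actual b, which may be near zero.

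**Step 4: does re-anchoring the baseline help?** If the intervention baseline is the verified history as of inclusion, e0 is about zero at both intervention readings. The remaining bias is the drift e1 − e0 in control lists. Stable control errors cancel in a difference of changes, and largely but not exactly in a ratio of means.

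**The case against.** The strongest reply is that a risk is being read as a fact. The article does not say which list is abstracted, whether the baseline reading is taken before or after the verified history is filed, or that the history overwrites existing entries. Such rules normally sit in the full protocol. Home-care patients are anchored at their first home visit, so the order of baseline and review may vary in that subgroup. Control clinics exclude only systematic involvement of an FMG pharmacist; physicians and nurses may update lists there. And because the outcome counts prescribed medications, a non-prescribed product found at interview should not enter it, while cancelling an unused but still active prescription is a real fall in the count.

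Most of this stands. It means the plan allows the artefact rather than guarantees it, and that only part of what verification changes would be bias. It does not remove the point, which rests on what the article states: the outcome source and a one-sided verification step filed in the chart. If baseline were abstracted after the review, the intervention baseline would be verified and the control baseline not, and drugs stopped at the review could be missed.

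A reader might go further and infer three things the document does not support:

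- That record cleaning will inflate the benefit. Removals and additions push in opposite directions, and no error rate is given.
- That no analysis of chart counts could separate the two components. The pharmacists' record of interventions can help to do so, and so can the verified history itself.
- That community pharmacy lists are untouched by the intervention. The care plan is made in collaboration with the community pharmacist, so those lists may be updated as well.

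**Conclusion.** The concern holds as a risk of differential measurement. As written, the plan lets correction of the medication list enter the group-by-time contrast for both primary outcomes. Neither direction nor size can be derived from the document. The only figure offered is an illustration: with two-sided alpha 0.05, an SD of change of about 3.14 back-solved from the stated power, and an assumed net clerical removal of 0.5 entries per intervention patient (half the target difference), the false-positive probability would be about 31% instead of 5%. The same net number of added entries would cut power for a true effect of 1 medication from 83% to about 31%. Nothing is quantified for the Beers count, because the article gives no design figure for it. The measurement rule should be settled before the outcome data are analysed.

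**What to change.** 1. In the intervention group, take the baseline count from the verified history as it stood at inclusion, before any pharmacist recommendation.
2. Use the pharmacists' record of interventions to code each change between the readings as an actual stop or start, or as a clerical correction, and do not count corrections as change.
3. Report the raw chart count at both dates as a sensitivity analysis.
4. Where consent allows, repeat the analysis with community pharmacy records obtained the same way in both groups at inclusion and at 6 months.

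**Cost and limits.** Items 1 to 3 need some extra abstraction from material the intervention already produces. Item 4 needs a pharmacy request per patient for two dates, some of them retrospective: by September 2022, 100 participants were enrolled (against 10 × 40 = 400 in the sample size calculation) and 23 had completed follow-up. The control list stays unverified, so the approach relies on its errors being stable over 6 months. Pharmacy lists may be partly updated in the intervention group, so they serve as a check rather than a neutral reference.
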